## Abstract

**Background:**

While most people faced with a terminal illness would prefer to die at home, less than a third in England are enabled to do so with many dying in National Health Service hospitals. Patients are more likely to die at home if their carers receive professional support. Hospice rapid response teams, which provide specialist palliative care at home on a 24/7 on-call basis, are proposed as an effective way to help terminally ill patients die in their preferred place, usually at home. However, the effectiveness of rapid response teams has not been rigorously evaluated in terms of patient, carer and cost outcomes.

**Methods/Design:**

The study is a pragmatic quasi-experimental controlled trial. The primary outcome for the quantitative evaluation for patients is dying in their preferred place of death. Carers’ quality of life will be evaluated using postal questionnaires sent at patient intake to the hospice service and eight months later. Carers’ perceptions of care received and the patient’s death will be assessed in one to one interviews at 6 to 8 months post bereavement. Service utilisation costs including the rapid response intervention will be compared to those of usual care.

**Discussion:**

The study will contribute to the development of the evidence base on outcomes for patients and carers and costs of hospice rapid response teams operating in the community.

**Trial registration:** Current controlled trials ISRCTN32119670.

## Background

While most people faced with a terminal illness would prefer to die at home [1,2], less than a third in England are enabled to do so with many dying in National Health Service (NHS) hospitals [2,3]. Given ideal circumstances, two thirds of terminally ill people would wish to die at home [2]. Many dying patients do not have effective choice over where they die. When professional support at home is available patients are more likely to die there [4,5]. The Department of Health policy guidance [6] stresses the importance of helping patients to achieve their wishes for place of death and the potential contribution of rapid response services to this cause.

Patients with life limiting conditions are often admitted to hospital because of a crisis or challenge that could not be resolved at home [7]. The crisis often stems from uncontrolled symptoms, carer fear or stress, not having medication available, or not having enough information about the patient’s prognosis or disease trajectory [7]. Research has shown that patients who spend more time in hospital or hospice during their illness are more likely to die there [5], therefore keeping patients out of inpatient facilities may help improve the likelihood that patients will be able to die at home. Rapid response teams providing palliative care respond quickly to crises and emergencies to help patients avoid admission to hospice or hospital. They integrate with routine community care and withdraw after the crisis has resolved, which may be death. They provide intense care for a few days at a time and operate on a 24/7 on-call basis. They are available at a time when the patient and/or carer are most vulnerable and when no other service is available or able to manage the crisis.

The effectiveness of rapid response teams has not been rigorously evaluated and there have been only three studies from the UK [8-10] which were descriptive evaluations, lacking control groups and two had small sample sizes (17 patients and 62 patients). The studies all identified above national average (21%) number of patients dying at home [3], 42%, 41% and 29%, and below national average use of institutional care. Thus rapid response services appear to prevent crisis admissions and increase the number of patients able to die at home, though these evaluations lack the power to provide an adequate evidence base without a control group.

It is important to evaluate new palliative care services in terms of patients’ preferences and service delivery costs, but it is also important to consider the impact of care in terms of carers’ quality of life and experiences. The Department of Health in the *End of Life Care Strategy*[6] discusses the concept of a good death and identifies key elements of the dying persons' experience, including dignity and respect, effective pain management, familiar surroundings and presence of family and friends. However it is not clear what factors are key to carers’ experiences.

The aim of the study is to contribute to the development of the evidence base on the consequences and costs of hospice rapid response teams, compared to usual care. It will also contribute to an understanding of the ways in which carers’ perceive and evaluate a ‘good death’.

## Hypotheses

The primary hypothesis, stated as a null hypothesis, is that rapid response services will lead to similar numbers of patients dying in their preferred place of death as is achieved with usual care. Secondary hypotheses address whether the rapid response service affects the quality of life of carers and whether there are cost savings from the rapid response service compared with usual care. In addition we aim to conduct a qualitative study to explore how carers perceive the quality of care and judge a ‘good death’.

## Methods/Design

### Study design

The quantitative evaluation of the rapid response intervention is a pragmatic quasi-experimental multi-centre controlled trial, with an embedded cost evaluation. The study also includes a qualitative evaluation using in-depth interviews to explore carers’ perceptions.

### Setting

The study is based at Pilgrims Hospices in East Kent which serves a community of 600,000 through three centres based in Canterbury, Ashford and Margate. The hospices each have an inpatient ward with 16 beds, a community outreach service and a day hospice. It receives approximately 2,000 referrals each year.

### Randomisation

The rapid response service will be rolled out sequentially in the three centres with six months between the start of provision in each site (Figure 1). A simple probabilistic randomisation method will be used to determine the order in which the three areas start the rapid response service. Once the intervention is introduced in an area, it will be available to all patients within the catchment area of that hospice, while usual services will continue to be offered in the control areas until the new service is rolled out in that area.

**Figure 1 F1:**
[figure not shown]
Time of service delivery by area.

The evaluation design randomises centres and therefore does not require the blind randomisation of individual patients into intervention or control group which would create serious ethical and practical problems. It is a design that protects from a number of potential sources of bias: contamination between patients, changes in health policy over time and resentful demoralisation of patients [11]. The design simultaneously addresses the situational and resource factors that arise from implementing an intensive new service across a wide area.

### Intervention

The rapid response service has been developed in line with best practice and following a complete literature review of the available evidence of hospice at home and rapid response services [12]. The main features of the service are that it:

· Is available to patients in their own home (including care homes);

· Has a robust ‘hospice standard’ assessment which takes account of: patient preferences, carer/family preferences, patient needs, and patient prognosis;

· Provides hands on care;

· Responds rapidly to crises using human and material resources available 24/7 with access to health care assistants, service coordinator, palliative care nursing, medical advice, and small pieces of equipment which can be carried by car; and

· Works in coordination with other community services.

### Patient evaluation

#### Inclusion criteria

All new referrals to the hospice who are assessed by a member of the hospice team during the study period are potentially eligible for inclusion in the study and may receive the intervention if available in their area. However, as the primary outcome measure is achieving the preferred place of death only those referred who die within the intervention or control period will be included in the analysis.

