#### Sample size

The primary outcome measure for the patient evaluation is death in the first recorded preferred place of death. In current 'usual' service provided by Pilgrims Hospices, approximately 29% of patients die in their preferred place of death. Increasing this figure to 60% will be equivalent to the gold standard framework for end of life care. In order to detect a difference of this magnitude, with alpha at 0.05 and 90% power, using a 2-sided test, requires data to be collected on 49 new patients per site per six month period. The design of the study involves 9 cells (Figure 1) so the total sample size is inflated to 441. This equates to 147 for each of the three sites and 147 for each six monthly period.

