#### Data collection

Data collection for the patient outcome will be conducted in a two stage process (Figure 2). First, patients will be entered onto a database after they have had their first assessment with a member of the hospice team. It is at this point that carers will be sent a questionnaire. Patient preferences will then be monitored while under hospice care in order to identify any changes in preferences over time. At the end of the study period, any patients still alive will be excluded as well as their carer. Patients who have died during the study period and who had a preferred place of death recorded in the hospice notes will be included. At this point, these patients’ preference data, place of death, diagnosis, demographic data and service utilisation data will be extracted from service records. Patients who died during the study period but did not have a preferred place of death recorded will be excluded from analysis, but carers of this group will be included.

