### Carer evaluation

Carers will be included in the study if they cared for a patient who died within the study period. Only one main carer per patient will be sampled.

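### The rule for which deaths are analysed is worded two ways and gives no arm to patients who straddle roll-out, so the arms can differ in referral-to-death time

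*Protocol article*

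**What the plan says.** Three parts of the protocol article decide who is analysed.

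- **Inclusion criteria:** "only those referred who die within the intervention or control period will be included in the analysis".
- **Data collection:** "Patients who have died during the study period and who had a preferred place of death recorded in the hospice notes will be included", and "At the end of the study period, any patients still alive will be excluded as well as their carer".
- **Carer evaluation:** "Carers will be included in the study if they cared for a patient who died within the study period".

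The Randomisation section fixes the timing. The service is "rolled out sequentially in the three centres with six months between the start of provision in each site", and "usual services will continue to be offered in the control areas until the new service is rolled out in that area". Once introduced, it is open to every patient in that catchment area.

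The patient Sample size section scores the first recorded preference and says "The design of the study involves 9 cells (Figure 1) so the total sample size is inflated to 441", that is, "147 for each of the three sites and 147 for each six monthly period". The patient Data analysis section specifies logistic regression with baseline values and cluster-robust standard errors. It names no term for calendar period or time since referral.

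**The concern.** A patient referred under usual care who dies after the site switches is an expected case in a staggered roll-out. Read strictly, the Inclusion criteria wording can leave that patient out. The Data collection wording keeps the patient in, and no arm is given.

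The time available to die also differs by arm. Control comes before intervention at every site and the study has one end date, so control referrals on average have longer in which to die and be counted. A crude comparison then sets longer survivors against shorter ones. Two results could be affected:

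- **Costs.** The economic evaluation gathers service use for as long as each patient is in the study and compares mean costs. A longer referral-to-death time adds cost directly.
- **Primary outcome.** Longer survival means an older first preference, and the article itself expects preferences to change.

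If the rule stays open, it could also be settled after the results are known.

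**Working it through.** **The plan's own figure.** With 29% v 60%, two-sided alpha 0.05 and 90% power, n = (1.960 + 1.282)² × (0.29×0.71 + 0.60×0.40) / 0.31² = 48.75, so 49 per cell, and 49 × 9 = 441. This reproduces, and the present point does not change it.

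**Inputs.** From the article: three sites, six-month steps, and nine cells (3 sites × 3 six-month periods = 18 months). Assumed, because the article does not give them: uniform referral, exponential survival with median m the same in both arms, and site starts at months 0/6/12 or 6/12/18 (Figure 1 is not shown).

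**Reading 1: arm by service at referral, death by study end.** Let λ = ln 2 / m. A referral in period 1, 2 or 3 has 12–18, 6–12 or 0–6 months left. With time left uniform on (a, b), b − a = 6:

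- share dying in time: p = 1 − (e^(−λa) − e^(−λb)) / (6λ)
- mean survival summed over those deaths, per referral: E = 1/λ − (1/6)[e^(−λa)(a/λ + 2/λ²) − e^(−λb)(b/λ + 2/λ²)]

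At m = 3 (λ = 0.231):

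| Referral period | p | E | mean = E/p (months) |
|---|---|---|---|
| 1 | 0.966 | 3.697 | 3.83 |
| 2 | 0.865 | 2.616 | 3.02 |
| 3 | 0.459 | 0.727 | 1.58 |

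With starts 0/6/12, control referrals fall over the periods as 2:1:0 site-periods and intervention referrals as 1:2:3.

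- Control: p = (2×0.966 + 0.865)/3 = 93%; mean = (2×3.697 + 2.616)/(2×0.966 + 0.865) = 3.58 months.
- Intervention: p = (0.966 + 2×0.865 + 3×0.459)/6 = 68%; mean = (3.697 + 2×2.616 + 3×0.727)/(0.966 + 2×0.865 + 3×0.459) = 2.73 months.

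With starts 6/12/18 the weights are 3:2:1 and 0:1:2. The same formulas give, as control v intervention mean months:

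| Assumed median | Starts 0/6/12 | Starts 6/12/18 |
|---|---|---|
| 1 month | 1.43 v 1.25 | 1.38 v 1.18 |
| 3 months | 3.58 v 2.73 | 3.35 v 2.28 |
| 6 months | 4.97 v 3.67 | 4.65 v 2.84 |

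Simulation agrees to within 0.02 month.

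**Within referral period.** Here p and E depend only on the time left to study end, which is the same at all sites. The arms therefore match within each period: 3.83 in both in period 1 and 3.02 in both in period 2. The overall gap is period imbalance, and a referral-period term removes it.

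**Reading 2: referral and death in the same arm's window (starts 0/6/12, m = 3).** Control patients now have 0–6 or 6–12 months.

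- Share included: (2×0.459 + 0.865)/3 = 59% control v 68% intervention.
- Mean: (2×0.727 + 2.616)/(2×0.459 + 0.865) = 2.28 v 2.73 months. The direction is reversed.
- Within period 1: control (0.727 + 2.616)/(0.459 + 0.865) = 2.53 v intervention 3.83. A period term does not remove this.

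**Patients who straddle roll-out (same assumptions).** Included control site-periods are 2.797 under reading 1 and 1.783 under reading 2. So (2.797 − 1.783)/2.797 = 36% of analysed controls die after their site has switched.

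**The case against.** The case on the other side has real force.

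- **The sections may not contradict each other.** The phrase in the Inclusion criteria can mean the two periods together, which is the study period. No sentence requires referral and death in one arm's window. This stands. It resolves the wording, but not the arm of a straddling patient or the lack of common follow-up.
- **Site and period terms cope.** A reader might infer that no adjustment can help because the selection runs with treatment. That is wrong under reading 1, where the gap vanishes within referral period. It holds only under reading 2.
- **The layout is assumed.** This stands. Starts at 0/6/12 leave one site with no control time, while the Discussion names a baseline period at all three sites as a research requirement. Under reading 1 the direction is the same in both layouts; under reading 2 it reverses.
- **No biased odds ratio is shown.** This stands. A reader might infer one, but the documents do not quantify any link between survival and achieving the preference.
- **Restriction to deaths is inherent.** True, since place of death exists only for those who die. The point concerns the window, not the restriction.
- **An article may leave this to a fuller document.** Partly true for straddling patients. But the article itself states who enters the primary analysis, and does so in two wordings.

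**Conclusion.** The point holds as a should-fix. The two sections need reconciling, and the article fixes neither a common referral-to-death window nor an arm for patients who straddle roll-out. With arm by referral and death by study end, the analysed controls survive longer on average by about 0.2 month at a median of 1 month, 0.8 to 1.1 at 3 months and 1.3 to 1.8 at 6 months. This rests on assumed exponential survival, uniform referral over 18 months and the two layouts above. If survival after referral is very short, the gap is small.

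The consequence for costs is direct. The consequence for the primary odds ratio is possible but unmeasured, and the documents do not support calling the trial's main result biased. A period term, which the stated model does not name, would deal with reading 1.

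**What to change.** Align the Inclusion criteria and Data collection sections on one rule for both arms, before analysis. Either option needs only referral, death and roll-out dates.

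**(a)** Assign arm by the service on offer at referral, include deaths by study end, and add referral period to the model. The periods should break at the roll-out dates, and the cost comparison needs the same adjustment. Cost: little beyond wording, but controls who die after the switch stay in the control arm although the new service is by then open to them (36% of analysed controls in the example above).

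**(b)** Include deaths within a fixed W days of referral, counting only referrals whose whole window lies in one service condition and before study end. Choose W from pre-trial hospice records and analyse the other deaths as sensitivity. This also equalises time for the cost comparison. At W = 3 and m = 3 months, mean referral-to-death is 4.33 − 3/(2 − 1) = 1.33 months in both arms.

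Cost of (b): later deaths and referrals near a switch leave the primary set. With 2,000 referrals a year (55.6 per site-month) and starts 0/6/12, eligible site-months are 0 + 3 + 9 = 12 control and 15 + 9 + 3 = 27 intervention, or about 667 and 1,500 referrals. Half die within three months at a median of 3, leaving about 335 and 750 deaths. At a median of 6 the share is 1 − 2^(−0.5) = 29%, leaving about 195 and 440. These counts are before a recorded preference is required, and compare with 441 planned in total.

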#### Sample size

The primary outcome measure for the patient evaluation is death in the first recorded preferred place of death. In current 'usual' service provided by Pilgrims Hospices, approximately 29% of patients die in their preferred place of death. Increasing this figure to 60% will be equivalent to the gold standard framework for end of life care. In order to detect a difference of this magnitude, with alpha at 0.05 and 90% power, using a 2-sided test, requires data to be collected on 49 new patients per site per six month period. The design of the study involves 9 cells (Figure 1) so the total sample size is inflated to 441. This equates to 147 for each of the three sites and 147 for each six monthly period.

#### Clinical outcomes

Preferences and any changes in preference will be ascertained by hospice nurses or doctors undertaking community, inpatient or clinic based assessments. Actual place of death will also be recorded.

#### Data collection

Data collection for the patient outcome will be conducted in a two stage process (Figure 2). First, patients will be entered onto a database after they have had their first assessment with a member of the hospice team. It is at this point that carers will be sent a questionnaire. Patient preferences will then be monitored while under hospice care in order to identify any changes in preferences over time. At the end of the study period, any patients still alive will be excluded as well as their carer. Patients who have died during the study period and who had a preferred place of death recorded in the hospice notes will be included. At this point, these patients’ preference data, place of death, diagnosis, demographic data and service utilisation data will be extracted from service records. Patients who died during the study period but did not have a preferred place of death recorded will be excluded from analysis, but carers of this group will be included.

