#### Sample size

The primary outcome measure for the carer evaluation is quality of life, measured using SF12 [14], at patient intake to hospice services and 8 months later. A clinically important change for quality of life is estimated as a 5 point change on the SF12. This equates to a medium effect size difference between the groups of 0.5. In order to establish an effect size difference of this magnitude at 80% power, with alpha at 0.05 requires 56 people within each of the intervention and control cells of the study. Previous experience with similar populations suggests 50% will refuse consent and the follow up rate at 8 months will be of the order of 70%. This inflates the required sample of potential carers to 160 in each cell of the study design, a total of 1440. Assuming that 40% of end of life patients have no primary carer the numbers seen over the study period based on current referral rates allow for a potential recruitment population of 1800.

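### Carers are excluded if the patient is alive at study close, although their SF12 outcome needs no death; under a one-way roll-out this selects carers unequally by arm

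*Protocol article*

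**What the plan says.** All references are to the protocol article.

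- Patient evaluation, Data collection: "At the end of the study period, any patients still alive will be excluded as well as their carer". The Carer evaluation section repeats the rule as an inclusion criterion: "Carers will be included in the study if they cared for a patient who died within the study period".
- Patient evaluation, Inclusion criteria, gives the only reason for requiring a death: "as the primary outcome measure is achieving the preferred place of death only those referred who die within the intervention or control period will be" analysed. That reason is specific to the patient outcome.
- Carer evaluation, Sample size: the carer primary outcome is "quality of life, measured using SF12 [14], at patient intake to hospice services and 8 months later". The clock starts at intake, not at death.
- Carers enter at the patient's first assessment, before survival is known: "It is at this point that carers will be sent a questionnaire".
- Randomisation: "The rapid response service will be rolled out sequentially in the three centres with six months between the start of provision in each site", and "usual services will continue to be offered in the control areas until the new service is rolled out in that area". Each site changes over once.
- Carer evaluation, Data analysis: the covariance analysis adjusts for baseline values and carer burden. It names neither bereavement status nor calendar period.

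The article already separates the two populations elsewhere. Carers of patients who died without a recorded preference stay in, although those patients do not.

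**The concern.** A requirement that makes sense for place of death has been carried over to an outcome that does not need it. It does not produce a bereaved-carer population either, because it tests for death at a calendar date and not at the carer's own follow-up. Take an 18-month study:

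- Patient referred in month 1, dies in month 12. The carer's 8-month form falls in month 9, while still caring. The carer is **kept**.
- Patient referred in month 17, dies in month 19. The 8-month form falls in month 25, after bereavement. The carer is **dropped**.

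Inclusion thus depends on an event after enrolment whose chance of being seen depends on how close intake is to study close. In a one-way roll-out, that distance is tied to arm. At stake are the comparability of the carer groups at the 8-month SF12 and the number of enrolled carers left to analyse.

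**Working it through.** **1. The plan's own figures.** Required carers: 56 / (0.5 × 0.7) = 160 per cell, × 9 cells = 1,440. Pool: 2,000 referrals a year × 1.5 years × 0.6 with a carer = 1,800. Both reproduce. The 1.5 years is inferred from three six-month periods. The inflation covers refusal and loss to follow-up, but not carers dropped because the patient is alive at close. Meeting 1,440 from 1,800 needs 1,440 / 1,800 = 80% of patients to die before close.

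**2. Assumptions.** The article gives no survival figures and Figure 1 is not shown. I assume uniform referral over 18 months, the same exponential survival in both arms (no service effect), arm fixed at referral, and one close at month 18. Service starts are at months 0/6/12 or 6/12/18.

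**3. Share dropped, 3-month median.** With λ = 3 / ln 2 = 4.328, a patient with r months left before close is alive at close with probability exp(−r/λ). Let G(r) = λ(1 − exp(−r/λ)), the integral of that probability from 0 to r: G(6) = 3.2461, G(12) = 4.0576, G(18) = 4.2605.

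- Starts 0/6/12, intervention (36 site-months, remaining time 0–18, 0–12 and 0–6): (4.2605 + 4.0576 + 3.2461) / 36 = 32.1%.
- Starts 0/6/12, control (18 site-months, remaining time 12–18 and 6–18): (0.2029 + 1.0144) / 18 = 6.8%.
- Starts 6/12/18, intervention (18 site-months): (4.0576 + 3.2461) / 18 = 40.6%.
- Starts 6/12/18, control (36 site-months): (0.2029 + 1.0144 + 4.2605) / 36 = 15.2%.

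About 56% of the dropped carers would already be bereaved at their 8-month form.

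**4. Bereaved at 8 months among kept carers.** This is the mean of F(min(r, 8)) divided by the mean of F(r), where F(t) = 1 − exp(−t/λ). Without the rule it is F(8) in both arms.

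| Median survival | Starts | Dropped, control v intervention | Bereaved among kept, control v intervention | Gap (points) | Both arms, no rule |
|---|---|---|---|---|---|
| 1.5 months | 0/6/12 | 0.8% v 17.6% | 98.1% v 99.2% | 1 | 97.5% |
| 1.5 months | 6/12/18 | 6.4% v 23.2% | 98.4% v 99.6% | 1 | 97.5% |
| 3 months | 0/6/12 | 6.8% v 32.1% | 89.9% v 95.2% | 5 | 84.3% |
| 3 months | 6/12/18 | 15.2% v 40.6% | 91.3% v 98.0% | 7 | 84.3% |
| 6 months | 0/6/12 | 24.0% v 51.1% | 78.7% v 89.0% | 10 | 60.3% |
| 6 months | 6/12/18 | 33.1% v 60.1% | 81.2% v 95.6% | 14 | 60.3% |

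A 24-month study with starts 6/12/18, and Weibull survival with shape 0.6, give the same direction under these definitions of arm and close.

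**5. Carer pool.** At a 3-month median, 1,800 × (1 − 4.2605 / 18) = 1,374, which is 66 short of 1,440. At 2 months about 1,512 remain, which is enough; at 6 months about 1,042.

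**6. Size on the SF12 scale.** The documents do not say how bereavement moves SF12. Suppose bereaved and still-caring carers differ by the full 5 points that the article calls clinically important. The bias is then the gap in bereaved share × 5: 0.053 × 5 = 0.27 points at a 3-month median (starts 0/6/12), and 0.144 × 5 = 0.72 points in the widest row of the table.

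**The case against.** **Direction.** A reader might infer that kept intervention carers are always bereaved more often, and for longer. The documents do not support that, because they do not say how a carer is assigned to an arm when the service reaches the area after referral. The Inclusion criteria section speaks of dying within the intervention or control period, which could mean the patient's own period. On that reading, at a 3-month median with starts 0/6/12, 41% of control and 32% of intervention carers are dropped, and 98% v 95% of those kept are bereaved, so both contrasts reverse. With starts 6/12/18 the direction stays but shrinks (32% v 41% dropped, 95% v 98% bereaved). If arm is instead set by service status at death or close, kept bereavement is 98% v 91% or 95% v 90%, higher in control. This objection stands. What survives it is that the rule selects carers unequally under every reading tried.

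**Size.** A reader might also infer that the SF12 comparison is seriously biased. Step 6 does not support that, and with survival near 1.5 months the bereavement gap is only about 1 point. This stands too, with one reservation: step 6 counts bereaved status only. Kept carers also differ somewhat in time since death (by about half a month at a 3-month median) and in whom they cared for (mean patient survival among those kept 3.6 v 2.7 months with starts 0/6/12).

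**Population.** A study of end-of-life care may reasonably want carers of patients who died. That is a legitimate target, but a calendar close does not define it; an equal window from intake would.

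**Conclusion.** The point holds in limited form and should be fixed, but it is not a fatal flaw. The carer exclusion has no stated reason that applies to carers, does not define a bereaved population, and selects carers differently by arm through the roll-out alone.

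With arm fixed at referral and one 18-month close, intervention carers are dropped more often: 7% v 32%, or 15% v 41%, at a 3-month median. The direction depends on that definition of arm and period. The bereavement gap runs from about 1 percentage point at a 1.5-month median to 10 to 14 at 6 months. The resulting SF12 bias cannot be derived from the documents but is probably well below 5 points. The loss of carers is the more tangible cost: at medians of 3 months or more the stated pool no longer covers the stated requirement. All sizes rest on assumed survival and on a layout inferred from the Randomisation and patient Sample size sections.

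**What to change.** In the Data collection and Carer evaluation sections, state that a carer's arm is fixed at the patient's referral. Replace the requirement that the patient died within the study period with a rule that does not depend on the calendar close: keep every main carer who returned a baseline questionnaire, whatever the patient's status at close. Leave the death requirement in place for the patient outcome.

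If the intended target is carers of patients who died, apply one equal window to all carers: the patient died before that carer's 8-month questionnaire. This removes the imbalance caused by the calendar, but it still conditions on survival after enrolment and is open to bias if the service affects survival. The text should say so.

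The cost is a change of wording and some extra follow-up postings. Baseline questionnaires already go out at first assessment, and late-referred carers who are kept already need follow-up past an 18-month close. Under the all-carer rule, the primary carer result covers bereaved and still-caring carers together.
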